score  $\geq 3$ ), an unfavourable interleukin 28 B genotype and a high baseline HCV viral load. The study results confirmed the efficacy of iSIL in a difficult-to treat patient group and underscored that iSIL could be a valuable treatment-option in patients not responding to PR (12). The potential role of iSIL as rescue therapy in patients not responding to previous combined therapy with PR and a HCV-specific PI was demonstrated by Biermer et al., 9 of the 13 responder patients are in the follow-up period: 3 of them achieved SVR24, 2 achieved SVR12, and 4 had a viral relapse (13). Recent reports also show the efficacy of iSIL in patients with HCV-reinfection after liver transplantation. After 14 days treatment of iSIL in a dosage of 20mg/kg all four patients showed normalization of liver enzymes and a significant decline of HCV-RNA with a mean log-reduction of 2.8 (14). Moreno et al. presented their data about the safety and the anti-HCV activity of a rescue therapy with iSIL in cirrhotic HIV-HCV co-infected individuals at the 19th conference on retroviruses and opportunistic infections (CROI) in 2012. They treated 4 individuals with previous partial response (PR) or relapses to PR with iSIL 20mg/kg for at least 14 days. Three patients started iSIL during PR and nitazoxanide (add-on strategy). Overall, therapy with iSIL led to negative HCV-RNA in 3 subjects and values  $<50$  IU/mL in the remaining. The period of mono-therapy with iSIL produced a time-dependent effect: the mean decrease of HCV-RNA was  $-2.5 \log_{10}$  IU/ml after 1 week and  $-4.62 \log_{10}$  IU/ml after 35 days. However, HCV-RNA rebounded in 4 patients after stopping iSIL. There were no significant adverse events related to iSIL and all patients maintained current antiretroviral therapy (ART) with undetectable HIV RNA (15).

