#### **4.5 Dose Rationale**

All included study-subjects will receive a lead-in therapy with iSIL in a dosage of 20mg/kg/day (expressed as silibinin concentration) once a day for 14 days. At the end of the THISTLE study, i.e. after the day of completion of the 14-day iSIL administration (day 15), the patients will be considered for eligibility to receive standard of care TT with telaprevir (i.e. 12 weeks combination therapy with telaprevir plus PR followed by 36 weeks of PR).

The rationale of 20mg/Kg/day is the observation, that there exist a strong dose-dependent effect with a greatest HCV-RNA decline when iSIL is administrated in a dose of 20mg/kg, whereas the lower dose (5, 10 or 15mg/kg) led to a significant lower HCV-RNA decline (16). iSIL dose-dependently reduced and even completely eradicated the HCV load, with the dose of 20 mg/kg per day being clearly the most effective dose.

Since effective antiviral concentration cannot be reached with the oral administration with the available formulations of silymarin/silibinin, the drug needs to be administrated intravenously. The rationale to use 14 days of treatment is a trade-off between virological efficacy of this treatment and logistic and financial constraints. Previous reports (10, 16) demonstrated a continuous decline during 2 weeks of iSIL therapy with a mean decline of 3 logs IU/ml in HCV-RNA. We assume that this decline would substantially improve the chances of SVR as this reduction of viral load should both increase the efficacy of PR and reduce the odds of drug resistance to telaprevir.

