## 6 STUDY DESIGN AND COURSE OF STUDY

### 6.1 General Design

This study is a multicentre, open-label, interventional study including HCV-HIV co-infected individuals with chronic HCV-genotype 1 infection and documented previous null-response (NR) or partial-response (paR) to standard therapy with SOC and progressed liver fibrosis.

The overall study-duration is 15 days. The first part is the once a day administration of iSIL from day 1 to 14. Since the half-life ( $T_{1/2}$ ) of the administrated study-drug is very short (3 hours), the follow-up of the study-subjects is one day (day 15) and the final visit will be on day 15.

Subsequent to THISTLE (at day 15) we have the intention to include the study-subjects in the SHCS trial # 688. The trial # 688 will investigate the occurrence of HCV-resistance to the HCV-PIs during TT. The duration of the # 688 will contain 48 weeks with a follow-up of 24 weeks. Importantly, we plan to review the results from the THISTLE trial with the data from the SHCS # 688.

The estimated time frame is listed below:

- Submission to ethical committee (Zurich as lead ethical committee): November 2012
- Ethical approval: January 2013
- Swissmedic approval: February 2013
- First patient enrolled: April 2013
- Enrolment: April 2013 to December 2013
- Last patient enrolled: End of December 2013

All included patients will receive a lead-in therapy with iSIL in a dosage of 20mg/kg/day for 14 days followed by standard of care TT. As mentioned above, the follow-up period will contain for one day due to short half-life time of the administrated study-drug. Moreover, a prolonged follow-up period outside THISTLE trial is warranted due to the SHCS trial # 688.

The included patients are HCV-HIV co-infected SHCS participants with chronic HCV-genotype 1 infection and documented previous null-response (NR) or partial-response (paR) to standard therapy with SOC and in urgent need of treatment (i.e. METAVIR fibrosis score  $\geq 2$  or ISHAK fibrosis score  $\geq 4$  or fibroscan stiffness  $\geq 9.5$  kPa). As cut-offs for the fibroscan we used the ones proposed in a recent review by Castera et al (17). NR is defined as less than 2 log10 IU/ml decrease in HCV RNA level from baseline at 12 weeks. paR is defined as more than 2 log10 IU/ml decrease in HCV-RNA level from baseline at 12 weeks of therapy but detectable HCV-RNA at weeks 12 and 24.

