### 9.16 Day 15 (visit 16, end of THISTLE)

- Documentation of adverse events
  - use the electronic CRF
- Concomitant medication
  - use the electronic CRF
- Physical examination
  - Including blood pressure while sitting (right/left), pulse rate, temperature (degree Celsius), cardiac auscultation, chest auscultation, abdominal auscultation, brief neurological examination
- Safety laboratory: full blood count, electrolytes (sodium, potassium), ASAT, ALAT, total and fractionated bilirubin, gamma GT, alkaline phosphatase, creatinine, albumin, total protein, INR
  - 10ml Heparin blood
- Pregnancy test:
  - 10ml Heparin blood
- HCV-RNA, HIV-RNA
  - 10ml EDTA blood
- CD3/4/8 count
  - 3ml EDTA blood
- Plasma aliquot as backup-blood for potential later analysis
  - 10ml EDTA blood
- PBMC: only at the study site Zurich
- Silibinin drug-level T24 (i.e 24 hour after the end of last silibinin infusion)
  - Blood (6 ml) must be collected in ACD (acid citrate dextrose) solution vacutainer tubes. The tubes containing ACD solution should be stored at +4°C. Tubes must be identified with the patient ID number and sample number as soon as blood has been collected
  - Blood samples must be brought to the laboratories without delay (maximum 30 min after blood collection).
  - Treatment of samples: centrifugation at 1500g for 10 min at +4°C. In a class II biohazard hood plasma (obtained after centrifugation) should be divided in three labelled tubes (of approximately 1mL each) ready for freezing at -80 ° C, within one hour after collection. If this deadline cannot be met, please keep the sample at 4° C until centrifugation and freezing.
- Accepted time window: at least one day after the end of iSIL administration

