## **12 STATISTICS**

### **12.1 Statistical and Analytical Plans**

The analyses of the primary and secondary endpoints of this non-comparative study will be purely descriptive. The average decline of HCV RNA during the lead-in phase (day +1 to day +15) will be expressed in  $\log_{10}$  IU/ml using methods for left-censored data (Tobit regression) (18) in case of undetectable values are encountered and represents the primary efficacy analysis and will be performed in the evaluable patients. We will further report the percentages (with 95% CI) of patients achieving undetectable levels of HCV RNA at the various time points. We will also attempt to analyse factors associated with  $\log_{10}$  HCV RNA response with mixed effects models (19) taking into account all measured HCV values from day -14 to day + 15. In these models, slopes will be allowed to change at day+1 and day +15. Potential co-factors will be first assessed in univariable and bivariable models to detect interactions and collinearities. Relevant effect modifiers and confounders will then be included in multivariable models. The following co-factors will be considered: age, gender, IL28B genotype, BMI, CD4 values and HIV RNA. We will look at the potential co-factors in univariable models first and only include relevant confounding variables in the multivariable analysis. Safety analyses will be performed including all patients that received at least one dose of the study medication (Safety Population). Adverse events will be reported in percentages (with 95% CI) of patients experiencing an event (for clinical events and abnormal laboratory values considered clinically significant by the Investigator – this represent the primary safety analyses) or the percentages below/above 1x and 2x normal range limits for laboratory values.

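### The exploratory HCV-RNA mixed model places its second slope change at day 15, the last sample, so that slope cannot be estimated and the whole treatment phase is fitted by one straight line.

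*Protocol*

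**What the plan says.** Section 12.1 has two separate efficacy analyses. The primary one is a Tobit regression of the average log10 HCV RNA decline from day 1 to day 15. The other is an attempted mixed-model analysis of factors associated with response (age, gender, IL28B genotype, BMI, CD4 and HIV RNA), "taking into account all measured HCV values from day -14 to day + 15". For the mixed models the section fixes the knots: "In these models, slopes will be allowed to change at day+1 and day +15".

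The study schedule takes HCV-RNA at screening and then daily from day 1 to day 15. Section 6.1 states that "the final visit will be on day 15". Section 9.16 sets the window for that visit as: "Accepted time window: at least one day after the end of iSIL administration".

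On the expected shape of the curve, section 4.4 cites a report in co-infected patients in which iSIL alone lowered HCV RNA by a mean of 2.5 log10 at one week and 4.62 log10 at day 35. It also describes one co-infected patient who fell from 126,000 to 78 IU/ml in one week of iSIL alone. Section 4.5 says that earlier reports "demonstrated a continuous decline during 2 weeks of iSIL therapy with a mean decline of 3 logs IU/ml in HCV-RNA".

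**The concern.** A knot is useful only if there are data on both sides of it. The knot at day 1 has screening on one side and treatment on the other. The knot at day 15 has nothing after it, so the model carries a slope that cannot be estimated. There is also no knot between day 1 and day 15, where 15 of the 16 scheduled samples per patient lie.

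The mixed model is the only planned analysis that models slopes over time. As specified, it cannot show any change of slope during treatment. If the decline is fast and then slow, the single slope describes neither phase. A co-factor that acts mainly on one phase would be judged only by its effect on the average slope. The knots and the data window are both written into the protocol, so this is not a detail left open for a later plan.

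**Working it through.** **1. Is the day-15 slope estimable?** The linear-spline design is [1, t, (t-1)+, (t-15)+], with t = -14, 1, 2, ..., 15 from the schedule.

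| Knots | Columns | Rank |
|---|---|---|
| 1 and 15 | 4 | 3 |
| 1 only | 3 | 3 |
| 1 and 8 | 4 | 4 |

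The column (t-15)+ is zero in every row. It stays zero when 20 patients are stacked with screening varied over -14 ± 7 days. Knots (1, 15) and knot (1) give identical fitted values, so the second knot adds nothing.

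**2. What do the background figures imply?**
- Week 1 (section 4.4): 2.5 / 7 = 0.357 log10/day.
- Days 7 to 35 (section 4.4): (4.62 - 2.5) / 28 = 0.076 log10/day, slower by a factor of 0.357 / 0.076 = 4.7.
- Interpolated two-week fall: 2.5 + 7 × 0.0757 = 3.03 log10, close to the 3 log10 in section 4.5.
- A constant slope reaching 3.0 at two weeks would give 1.5 at one week, against 2.5 reported. The single case fell log10(126,000 / 78) = 3.21 in one week.
- A constant slope at the week-1 rate would give 5.0 at two weeks, against about 3.

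**3. What would the planned model do with such a curve?** Assume a mean change of 0 at screening and day 1, -2.5 at day 8 and -3.03 at day 15, linear between these points. The least-squares fit with the one effective knot (day 1) is:

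| Quantity | Assumed curve | Planned model |
|---|---|---|
| Slope, days 1 to 8 (log10/day) | -0.357 | -0.216 |
| Slope, days 8 to 15 (log10/day) | -0.076 | -0.216 |
| Level at day 1 | 0 | -0.46 |
| Level at day 8 | -2.50 | -1.97 |
| Level at day 15 | -3.03 | -3.49 |
| Slope before day 1 (log10/day) | 0 | -0.46 / 15 = -0.031 |
| Day 1 to day 15 fall | 3.03 | 3.49 - 0.46 = 3.03 |

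The largest miss is 0.53 log10, at day 8. The total fall is recovered because the assumed break is at the midpoint of days 1 to 15, so the fitted slope is the average of the two true slopes.

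**4. How sensitive is this to the two-week fall?** With 2.5 log10 kept at day 8:

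| Two-week fall (log10) | Largest misfit (log10) |
|---|---|
| 2.8 | 0.59 |
| 3.0 | 0.53 |
| 3.5 | 0.40 |
| 4.0 | 0.27 |
| 5.0 | 0 |

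**5. Does a knot inside treatment help, and does its position matter?** On the curve of step 3, knots (1, 8) reproduce the curve exactly, as they must, because the curve was built to break at day 8. Knots (1, 3) give slopes of -0.603 and -0.187 and a day 1 to day 15 fall of 3.45 instead of 3.03. The position therefore matters.

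**The case against.** **The primary endpoint does not depend on this model.** A reader might infer that the kinetics endpoint is compromised. The documents do not support that. Section 5.1 defines the endpoint as the difference from day 1 to day 15, and section 12.1 assigns it to the Tobit regression, which uses no knots. The mixed model is an attempted co-factor analysis in a descriptive study. This objection stands in full.

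**The redundant knot is harmless numerically.** This is correct: the zero column can be dropped and the fit is unchanged. What remains is the consequence of having no knot inside treatment.

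**The evidence for two phases is thin.** A reader might infer that the protocol's own data refute a straight line. They do not go that far. The co-infected report has 4 patients, three of whom started iSIL during other therapy. Its second time point, day 35, lies outside this 14-day course, and the week-2 rate is an interpolation. All four patients ended negative or below 50 IU/ml, so part of the slowing could be an assay-floor effect. Section 4.5 speaks only of a continuous decline. The figures suggest a fast and then slow pattern but do not establish it.

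**The day-8 error should not be read as a full log.** The fitted day 1 to day 8 fall is 1.97 - 0.46 = 1.5 against 2.5, but that comparison counts the day-1 misfit as well. The level at day 8 is wrong by 0.53.

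**The day-15 window is open upward.** A few late samples could make the last slope formally estimable. If 1 to 5 of 20 patients were sampled at day 16, its standard error would be about 42 to 19 times that of the slope change at day 1 (assuming independent errors). Section 12.1 in any case ends the data at day +15.

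**Conclusion.** The point holds for the exploratory mixed model. The slope after day 15 is not estimable, and the treatment phase is restricted to one line. Both follow directly from section 12.1 and the schedule and need no assumption.

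The size of the misfit is conditional. It rests on a fall of 2.5 log10 at one week and about 3 log10 at two weeks, taken from small and mixed groups, with a break at day 8. On that basis the single slope of -0.22 log10/day stands in for about -0.36 and then -0.08, the curve is missed by up to about 0.5 log10, and a false pre-treatment decline of about 0.03 log10/day appears. The loss of co-factor effects specific to one phase follows from the model's form; its size was not calculated.

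The primary Tobit analysis is untouched, and on this curve the planned model still returns the correct total fall.

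**What to change.** In section 12.1, replace the day-15 knot with at least one pre-specified knot inside days 1 to 15. About day 8 is a reasonable choice because it is the one-week point for which the background gives a figure. Name another position as a sensitivity analysis, since step 5 of the working shows that the slopes depend on it. Keep the left-censored random-effects approach already cited there. Report the early and late slopes, and the co-factor effects on each. Leave the Tobit day 1 to day 15 decline as the primary efficacy analysis, and do not replace it with a decline derived from the mixed model.

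The text change is about one sentence, with no new samples, visits or patients. The cost is one more slope term and its co-factor interactions, so co-factor estimates will be somewhat less precise with 20 patients.

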### 4.1 Background and Rationale

Chronic hepatitis C virus (HCV) is a major cause of morbidity and mortality worldwide with an estimated number of 180 million infected patients. HCV infection causes around 376'000 deaths per year due to complications like hepatocellular carcinoma (HCC) and endstage liver disease (1). In Switzerland, 50'000-70'000 individuals are HCV infected (2). HCV-HIV co-infection is reported in approximately 30% of all Swiss HIV Cohort Study (SHCS) participants (3). In 2010, almost 100 liver transplantations have been performed, 25% of them because of HCV-related endstage liver disease (4).

Until 2012 the current standard treatment of patients with chronic hepatitis C was a 24 to 72 weeks therapy with pegylated interferon- $\alpha$  and ribavirin (PR). Response to the treatment with PR depends on the HCV-genotype, HCV-HIV co-infection, baseline hepatitis C viral load, interleukin 28 B genotype, sex and stage of fibrosis (5). Sustained virological response (SVR) after treatment with PR can be achieved in 30% to 80% in treatment-naïve patients, depending on host and viral characteristics.

In 2012, the protease-inhibitors (PI's) telaprevir and boceprevir as first directly acting HCV drugs have been approved by Swissmedic for hepatitis C mono-infected and HCV-HIV-co-infected individuals. However, therapy success is strongly limited in null-responders (NR) to previous PR. NR is defined as a reduction of  $< 2\log_{10}$  in HCV RNA after 12 weeks of therapy. Of note, in patients with previous failure to PR, TT is in fact a mono-therapy with a high risk of rapid development of resistance against the PI's. Treatment of HCV-HIV co-infected individuals with the new PI's is accompanied by additional challenges including drug-drug interactions, toxicity, and a high pill burden which impedes drug adherence.

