#### Exclusion criteria:

- contraindications to the study drug under study, e.g. known hypersensitivity or allergy to any ingredient of the study drug,
- women who are pregnant or breast feeding,
- intention to become pregnant during the course of the study,
- lack of safe contraception, defined as:  
Female subjects of childbearing potential, not using and not willing to continue using a medically reliable method of contraception for the entire study duration, such as oral, injectable, or implantable contraceptives, or intrauterine contraceptive devices,

or who are not using any other method considered sufficiently reliable by the investigator in individual cases.

Please note that female subjects who are surgically sterilized/hysterectomized or post-menopausal for longer than 2 years are not considered as being of child bearing potential.

- Male patients who do not agree to abstain from intercourse or who do not use a condom
- other clinically significant concomitant unstable disease states (e.g., renal failure, unstable cardiovascular disease),
- known or suspected non-compliance, drug or alcohol abuse,
- inability to follow the procedures of the study, e.g. due to language problems, psychological disorders, dementia, etc. of the subject,
- participation in another study with investigational drug within the 30 days preceding and during the present study,
- previous enrolment into the current study,
- enrolment of the investigator, his/her family members, employees and other dependent persons
- Patients in need of ART with HIV virological failure ( $\geq 400$  copies/ml) in the last 3 months
- Any other condition that, in the opinion of the Investigator, may jeopardize the study conduct according to the protocol.

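### The exploratory co-factor search in section 12.1 selects from up to 21 looks in about 20 patients and omits baseline HCV RNA, fibrosis stage and prior response type

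*Protocol*

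**What the plan says.** Protocol section 12.1 introduces the analysis with "We will also attempt to analyse factors associated with" HCV RNA response, using mixed effects models on all HCV RNA values from day -14 to day 15. The candidates are fixed: "The following co-factors will be considered: age, gender, IL28B genotype, BMI, CD4 values and HIV RNA".

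So is the way they are handled. The first step is a screen: "Potential co-factors will be first assessed in univariable and bivariable models to detect interactions and collinearities". The second step carries forward what the screen has picked out: "Relevant effect modifiers and confounders will then be included in multivariable models". The section then repeats that it will look at factors singly and "only include relevant confounding variables in the multivariable analysis".

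The same section says "The analyses of the primary and secondary endpoints of this non-comparative study will be purely descriptive". Section 12.2 gives hypotheses as not applicable, and no alpha or selection threshold appears. Section 12.3 aims for 20 evaluable patients.

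Section 4.1 says that response to PR depends on HCV genotype, HIV co-infection, "baseline hepatitis C viral load, interleukin 28 B genotype, sex and stage of fibrosis". Later in that section, high baseline load and advanced fibrosis appear again as unfavourable conditions for triple therapy. It also describes the success of protease-inhibitor treatment as much reduced in prior null-responders. Section 7.1 admits both null- and partial-responders.

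**The concern.** Two stated choices sit badly together with 20 patients.

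First, membership of the final model depends on how each factor looks in the same data. The 16 scheduled HCV RNA values per patient sharpen each patient's own slope, but age, gender, IL28B genotype and the other co-factors vary only between patients. For them the sample is about 20. Many looks on so few units yield chance findings, and the estimates that survive tend to be too large.

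Second, the list does not follow the protocol's own rationale. Two variable determinants named in section 4.1 are absent, as is the response type that defines entry, while age, BMI and CD4, which section 4.1 does not list as determinants, are present.

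At stake is the credibility of any statement about who responds to iSIL. Such a statement could be carried into the planned review of these data alongside SHCS trial 688.

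**Working it through.** The sample size in section 12.4 has no formula behind it and does not consider co-factors, so there is no figure of the plan's to reproduce.

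**Inputs**
- Co-factors: 6 (section 12.1).
- Pairs: 6 × 5 / 2 = 15, so up to 6 + 15 = 21 looks. This assumes that every pair is examined against the outcome.
- Patients: 20 (sections 12.3 and 12.4).
- Error per look: not stated. Assumed 5%, with 10% and 20% as a range.
- Between-patient SD of the decline: 1.01 log10, reading the ± 1.01 in section 4.1 as an SD (assumption).

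**Chance of at least one false signal if no factor matters**, 1 − (1 − a)^m, independent looks:

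| Error per look (a) | 6 single looks | 21 looks |
|---|---|---|
| 5% | 1 − 0.95^6 = 26.5% | 1 − 0.95^21 = 65.9% |
| 10% | 1 − 0.90^6 = 46.9% | 1 − 0.90^21 = 89.1% |
| 20% | 1 − 0.80^6 = 73.8% | 1 − 0.80^21 = 99.1% |

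The looks are correlated, so independence was checked by simulation: 4,000 null trials of 20 patients, four continuous and two binary co-factors, one response per patient, and 6 single-factor and 15 interaction tests by least squares. At 5% per look, at least one false signal occurred in 26.8% (6 looks) and 62.4% (21 looks) of trials, with on average 0.29 and 1.04 false signals per trial.

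**What 20 patients can detect** (80% power, two-sided 5%, no adjustment)
- Continuous factor: r = tanh(2.80 / √17) = 0.59.
- Binary factor, 10/10 split: 2.80 × 1.01 × √(1/10 + 1/10) = 1.27 log10 (1.34 with the t distribution).
- Binary factor, 15/5 split: 2.80 × 1.01 × √(1/15 + 1/5) = 1.46 log10 (1.55 with t).

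The mean decline cited in section 4.1 is 3.02 log10.

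**Why selected estimates are exaggerated.** At a 10/10 split and an observed SD of 1.01, a difference reaches p < 0.05 only above 2.10 × 1.01 × √0.2 = 0.95 log10. A true difference of 0.5 log10 is then selected in its own direction only when estimated at nearly twice its size.

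**Expected share of signals that are false**, with k real binary factors at a 10/10 split, 5% per look, m looks: 0.05(m − k) / [0.05(m − k) + k × power]. Power is 0.18, 0.55 and 0.88 for differences of 0.5, 1.0 and 1.5 log10.

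| Looks | Real factors | 0.5 log10 | 1.0 log10 | 1.5 log10 |
|---|---|---|---|---|
| 21 | 1 | 85% | 64% | 53% |
| 21 | 2 | 72% | 46% | 35% |
| 6 | 1 | 58% | 31% | 22% |
| 6 | 2 | 36% | 15% | 10% |

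**The list against section 4.1**

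| Determinant named for PR response | In this trial |
|---|---|
| HCV genotype | Fixed by eligibility (genotype 1) |
| HIV co-infection | Fixed by eligibility |
| IL28B genotype | Listed in 12.1 |
| Sex | Listed in 12.1 |
| Baseline HCV RNA | Varies, not listed |
| Fibrosis stage | Varies, not listed |

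Four of the six can vary, and two of those four are missing. Prior null versus partial response also varies and is not listed.

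**The case against.** The analysis is announced as an attempt, the study is descriptive, and neither primary endpoint depends on it. That stands and limits the weight of the point.

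No p-value rule is stated. Relevance may be judged otherwise or be defined in an analysis plan not shown, and part of the pairwise step looks for collinearity, which is not a test against outcome. So 21 is an upper count and 5% an assumption. A later threshold would not remove the problem, though: selection on the same 20 patients is already fixed in 12.1, and a looser threshold makes it worse.

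Baseline HCV RNA is partly in the model already, because the day -14 and day 1 values are modelled as outcomes. That is fair, but it does not by itself report whether baseline load is associated with the on-treatment slope. Fibrosis is harder to add than it looks, since section 7.1 accepts either biopsy or fibroscan and not every patient need have a current value on one scale. That stands.

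Four stronger readings might be inferred and are not supported:
- That the search will mostly pick noise. This depends on how many factors are real and how strong they are. With two real factors of 1 log10 or more, under half of the expected signals are false even with 21 looks.
- That the protocol ignores its own predictors. Two of the four that can vary are listed, and section 4.1 names all of them for PR, not for iSIL alone.
- That the omissions cause the false signals. They do not: adding two variables to the same screen would give 8 + 28 = 36 looks.
- That HIV RNA has too little spread to be useful. The exclusion covers "Patients in need of ART with HIV virological failure" at 400 copies/ml or more and sets no ceiling for patients not in need of ART. The untreated co-infected patient described in section 4.4 had measurable HIV RNA.

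**Conclusion.** The point holds for an exploratory analysis only. The stated procedure selects factors from up to 21 looks in about 20 patients. If no factor matters and each look is a 5% test, a false signal is more likely than not (62 to 66%); with the six single looks alone it is about 26%. Unadjusted, only effects of roughly 1.3 to 1.5 log10 for a binary factor are reliably detectable, so smaller real effects would be selected mainly when overestimated. These figures rest on the assumed error per look, on all pairs being tested against outcome, and on an SD of 1.01.

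Separately, the list leaves out baseline HCV RNA, fibrosis stage and prior response type, which the protocol's own background and entry criteria point to. The safety analysis and the average HCV RNA decline are untouched.

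**What to change.** Reword section 12.1 as follows.
- Replace the univariable and bivariable selection with a short fixed list. Add baseline HCV RNA, specified as a factor associated with the on-treatment slope, and prior null versus partial response. Add fibrosis stage if one scale is chosen for all patients. HIV RNA need not be dropped.
- Drop the pairwise interaction search.
- Report every listed factor's estimate with its 95% CI, whether or not it looks interesting, and label the results exploratory.

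A fixed list does not abolish chance findings: by the same formula, four factors give 1 − 0.95^4 = 18.5%. The gain is that the pairwise looks go, nothing is filtered on the data, and the reader sees how many factors were examined.

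The cost is a change of text. Baseline HCV RNA is measured on day 1 and prior response is documented at entry; only fibrosis needs a decision on scale. The downside is that interactions are not explored and no selected multivariable model is reported.
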